**Methods/design:**

This study will be a randomised controlled trial with a parallel-group design. A total of 60 eligible participants will be assigned to the Tuina group or healthcare education group (Education group) at 1:1 ratio using stratified randomisation with gender and age as factors. The interventions of both groups will last for 30 min per session and be conducted twice each week for 12 weeks. This study will primarily focus on pain evaluation assessed by detecting the changes in brain grey matter (GM) structure, white matter (WM) structure, and the cerebral functional connectivity (FC) elicited by Tuina treatment, e.g., thalamus, hippocampus, anterior cingulate gyrus, S1, insula, and periaqueductal grey subregions (PAG). The two groups of patients will be evaluated by clinical assessments and multimodal magnetic resonance imaging (MRI) to observe the alterations in the GM, WM, and FC of participants at the baseline and the end of 6 and 12 weeks’ treatment and still be evaluated by clinical assessments but not MRI for 48 weeks of follow-up. The visual analogue scale of current pain is the primary outcome. The Short-Form McGill Pain Questionnaire, Western Ontario and McMaster Universities Osteoarthritis Index, 36-Item Short Form Health Survey, Hamilton Depression Scale, and Hamilton Anxiety Scale will be used to evaluate the pain intensity, pain feeling, pain emotion, clinical symptoms, and quality of life, respectively. MRI assessments, clinical data evaluators, data managers, and statisticians will be blinded to the group allocation in the outcome evaluation procedure and data analysis to reduce the risk of bias. The repeated measures analysis of variance (2 groups × 6 time points ANOVA) will be used to analyse numerical variables of the clinical and neuroimaging data obtained in the study. *P*<0.05 will be the statistical significance level.

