### Sample size

Sample size is required to compare two group mean values. The calculation method of bilateral equality of two samples is adopted [56] for two groups of A = Tuina group and B = Education group. Suppose H0: μA−μB=0, H1: μA−μB≠0. According to previous relevant research and pre-experiment results [39, 57], we expect the VAS significant score difference between and after 12 weeks of Tuina as μA = 3, and the VAS score difference between and after healthcare education intervention as μB = 0.7, assuming that the standard deviation *σ* of the two groups is equal, i.e., *σ*=2.1. If we set *α*=0.05 as the type I error, *β*=0.10 as the type II error, and 1−*β*=0.90 as the power, the final result is that we need at least 25 samples in each group. For the primary outcome, VAS will be assessed at baseline and at the end of 6 and 12 weeks of treatment, followed by 12, 36, and 48 weeks of follow-up. The statistical significance is defined as *P* < 0.05, and the 95% confidence interval will be reported.

Many MRI studies have reported statistical significance with 12 to 21 patients per group [23, 58–60]. To have a powerful and repeatable statistical effect, we require 25 patients per group in this trial. Considering a 20% dropout rate and the possible excessive head motion during scanning, it will include 30 KOA participants in each group. In summary, we plan to enroll 60 participants, and each group will undergo MRI scans to investigate different central mechanisms between Tuina and healthcare education treatments.

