#### Primary outcome measurement

The primary outcome measurement is VAS [74]. VAS is used to assess the current degree of pain. VAS is a 10-point scale selected to quantitatively measure the level of KOA pain during the study, for which 0 means no pain and 10 means unbearable pain. The VAS mean scores will be assessed by repeated longitudinal analysis. The single timepoint of the primary interest for the comparison is week 12.

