### Statistical analyses

Clinical data will be analysed through the intention-to-treat assumption. For all outcomes, we use longitudinal models where participant outcomes and treatments are collected at a multiple follow-up times. Moreover, participants who meet the suspension criteria will be removed from the trial, and the modified intention-to-treat analysis will be adopted. For the missing data, several sensitivity analyses will be conducted to evaluate their effects on the results of the experiment. All analyses were performed with SPSS 21.0 statistical software (IBM, Armonk, NY, USA) by statisticians who are blinded to the group allocation.

The baseline characteristics will be expressed with descriptive statistics for the two groups, which are reported as the mean ± standard deviation. A Kolmogorov–Smirnov test with Lilliefors correction will be used to analyse all quantitative variables to determine whether they follow a normal distribution. Parametric statistics (Tukey test) or nonparametric statistics (Wilcoxon rank-sum test) will be used for the within- and between-group analyses in accordance with the results of the homogeneity and normality analyses. When the initial homogeneity and normality of data distribution are found, repeated-measure ANOVA will be implemented, or the Friedman test and Kruskal–Wallis test will be used when initial homogeneity but non-normality of data distribution is found, or only linear mixed model will be adjusted for age and gender if the initial homogeneity is not found. Adverse events in each group will be documented as percentage for safety assessments by using the chi-square test or Fisher’s exact test. Statistical significance is defined as *P* < 0.05, and the 95% confidence interval will be reported.

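### A normality test on the scores decides whether the primary VAS is analysed by a means-based model or by Friedman and Kruskal–Wallis tests, and the rank branch does not supply the estimate that the rest of the plan relies on.

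*Protocol article*

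**What the plan says.** The Statistical analyses section sets up the switch in two steps. First, "A Kolmogorov–Smirnov test with Lilliefors correction will be used to analyse all quantitative variables to determine whether they follow a normal distribution". The test is applied to the variables themselves; residuals are not mentioned. Then there are three branches:

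- Homogeneous and normal: "When the initial homogeneity and normality of data distribution are found, repeated-measure ANOVA will be implemented".
- Homogeneous, not normal: "or the Friedman test and Kruskal–Wallis test will be used when initial homogeneity but non-normality of data distribution is found".
- Not homogeneous: "only linear mixed model will be adjusted for age and gender if the initial homogeneity is not found".

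Other statements assume a longitudinal analysis of means. The same section says "For all outcomes, we use longitudinal models where participant outcomes and treatments are collected at a multiple follow-up times". The abstract says "The repeated measures analysis of variance (2 groups × 6 time points ANOVA) will be used to analyse numerical variables" and mentions no fallback. The sample size section opens with "Sample size is required to compare two group mean values" and plans on mean VAS changes of 3 and 0.7. The primary outcome section refers to VAS mean scores under a repeated longitudinal analysis, makes week 12 the time point of primary interest, and describes the measure thus: "VAS is a 10-point scale selected to quantitatively measure the level of KOA pain during the study". The sample size and statistical sections both say that a 95% confidence interval will be reported, without saying of what.

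**The concern.** If the VAS is homogeneous but fails the normality test, the plan leaves the model that its other sections describe. Friedman compares visits within one set of patients, so treatment arm does not enter it. Kruskal–Wallis with two arms is the rank-sum test at a single visit, so time does not enter it. Together they contain no test of whether the arms change differently, and they do not estimate the difference between mean changes on which the trial was sized.

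At stake is what the trial reports as its main result. The form of the primary estimate is not settled until the scores have been tested. Outcomes on similar scales could be analysed by different methods because one passed a normality test and another failed it. The result of such a test on a bounded, possibly rounded 0–10 score also says little about whether two means can be compared safely with 25 to 30 patients per arm.

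**Working it through.** **1. Inputs.** From the sample size section: mean changes 3 and 0.7 (difference 2.3), SD 2.1, two-sided alpha 0.05, power 0.90, 25 per arm before dropout and 30 after. From the outcome section: scale 0 to 10, week 12 primary. Not in the document, and therefore assumed: the mean VAS, the recording step, the correlation between visits (0.5), and whether normality is tested per arm, per visit or pooled.

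**2. The plan's own figure.** n per arm = 2(1.960 + 1.282)² × 2.1² / 2.3² = 17.5, so 18 (19 with the t distribution). The stated inputs do not reproduce 25. That is a separate matter, used here only to fix the available power. At 25 per arm the standardised difference is 2.3 / (2.1 × √(2/25)) = 3.87. Power is Φ(3.87 − 1.96) = 97.2%, or 96.7% with the t distribution.

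**3. How often the switch trips.** Simulated Lilliefors test at 5%, with an underlying score that is exactly normal, SD 2.1:

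| Recording | Assumed mean | n = 30 | n = 60 |
|---|---|---|---|
| Whole points | 5 | about 40–45% | about 80–85% |
| Steps of 0.1 | 5 (mid-scale) | about 4–6% | about 4–6% |
| Steps of 0.1, floor at 0 | 2 | about 25% | about 50–60% |

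The ranges cover repeated simulation runs. With whole points the rounding alone causes the failures. At 0.1 the test behaves nominally unless the mean is near 2.

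**4. The unit of testing.** Two arms by six visits give 12 cells. If any one failure counts, independent tests of truly normal continuous scores would trip the switch in 1 − 0.95¹² = 46% of trials; simulation with correlated visits gives 47%. The document does not say which unit applies.

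**5. Is the switch needed to protect the means-based test?** Whole-point 0–10 scores, 25 per arm. With both week-12 means at 2.5, the t-test's type I error is 4.7%. With means 2.5 and 4.8 (difference 2.3), power is 96.9% for the t-test and 96.4% for Kruskal–Wallis. The switch protects nothing that needs protecting.

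**6. Does the switch damage the week-12 test?** The two-stage rule (normality test, then t-test or Kruskal–Wallis) was simulated in 3,000 trials with an assumed baseline mean of 5.5 and correlation 0.5. Type I error was 5.2–5.7%, with simulation error of about ±1.96 × √(0.05 × 0.95 / 3000) = ±0.8 points. Power was about 96%. The rule does no material harm to the test.

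**7. What the rank branch can deliver.**

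| Commitment elsewhere | Friedman | Kruskal–Wallis, two arms |
|---|---|---|
| 2 × 6 ANOVA (abstract) | no arm term | no time term |
| Comparison of two means (sample size) | no | tests arms, estimates no mean |
| VAS mean scores, longitudinal (primary outcome) | ranks, not means | ranks, one visit |
| Week-12 comparison of arms (primary outcome) | no | yes, as a test |

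**The case against.** The strongest reply is that the plan is safer than it looks. Week 12 is fixed as the comparison, and a rank test of two randomised arms at that visit is valid and almost as powerful as the t-test. The switch is written down in advance and applied by statisticians blinded to allocation. If it is run on baseline scores, as the word initial suggests, it cannot depend on the treatment effect. A rank analysis can also carry its own interval for a shift in location. All of this stands, and it confines the point to the estimate and to consistency.

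Several stronger readings are tempting, but the document does not support them:

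- *That the three branches contradict each other.* They are mutually exclusive: homogeneity is settled first, then normality. Sending non-normal data to rank tests when homogeneous and to a mixed model when not is odd, but not a contradiction.
- *That a pooled Friedman test would be taken as evidence for Tuina.* The section speaks of within- and between-group analyses, so Friedman within arms and Kruskal–Wallis between arms is the natural reading. No pooled use is stated.
- *That entry at VAS 3 or more cuts off the baseline scores.* That criterion is average pain over three months; the outcome is current pain.
- *That the floor at 0 would trip the test at baseline.* For means of 4 or more, the floor alone gives about 4–6% failures. It matters only for means near 2, which is unlikely at entry.
- *That a mean difference with its interval was promised in those words.* The text promises a 95% confidence interval and does not name the quantity.

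**Conclusion.** The point holds in a limited form. The plan lets a normality test on the scores choose the primary analysis, and the rank branch does not match the longitudinal, means-based analysis described in the abstract, the sample size section, the primary outcome section and the statistical section itself. The cost is a primary estimate and interval that are not fixed in advance, and possibly different methods for similar outcomes.

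A reader might infer that the week-12 test would be invalid or underpowered. The calculations do not show that: type I error stays near 5%, and power stays near 96% at 25 per arm.

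The chance of entering the rank branch cannot be settled from the document. It also requires that homogeneity be found. Given that, the failure rate runs from about nominal (0.1 steps, mid-scale) to about 40–45% of samples of 30 and 80–85% of samples of 60 (whole points, SD 2.1, assumed mean 5). The description as a 10-point scale suggests whole points but does not establish them. The mismatch between the sections does not depend on these assumptions. This should be fixed, but it does not threaten the validity of the trial.

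**What to change.** In the Statistical analyses section:

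1. Delete the normality test as a means of choosing the method.
2. Name one means-based longitudinal model for the VAS, used whatever the distribution. The linear mixed model already mentioned there is suitable. State that the primary result is the between-arm difference at week 12 from that model, with its 95% CI.
3. Keep the rank-sum test, already named in the section, or a bootstrap interval at week 12 as a sensitivity analysis only.
4. Do not use Friedman as a test of treatment effect.
5. Apply the same rule to the secondary scales, and bring the abstract's description of the analysis into line.

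The cost is a change of wording. The model is already named in the plan, no new data are needed, and the sample size is unaffected: at 25 per arm the means-based comparison has about 97% power on the plan's own inputs.

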### Quality control

During the processing of the trial, quality control will be conducted with the management of the steering committee. To ensure the consistency of methods, professional trial method and regular monitoring technique should be trained before the researchers participate in the trial. If the study protocol is modified or corrected, the steering committee and ethics committee should be informed. The steering committee and ethics committee will ensure that the trial process works as planned, such as monitoring recruitment, potential harms, Tuina intervention, Education intervention, and data quality.

## Discussion

Chronic pain in KOA often seriously affects the patients’ quality of life. Alleviating joint pain is an important part of KOA treatment recommendations in the international OARSI guidelines (2014) [80] and the Chinese Osteoarthritis Diagnosis and Treatment Guidelines (2018) [1]. Chronic pain of KOA is not completely consistent with the clinical imaging performance of the knee joint, meaning that the results of knee X-rays should not be used in isolation when assessing individual patients with knee pain [81]. KOA also reportedly has a high probability of pain after successful operation [82]. The reason may be the key role of the brain as the integration centre of neural signals [83]. This study will provide a more powerful evidence-based proof for Tuina therapy in KOA patients with chronic pain through the possible study outcomes and benefits of longitudinal data.

Tuina belongs to the key noninvasive and nondrug therapies of TCM with distinctive characteristics [84, 85], which is used for pain relief in KOA for more than a thousand years in China and some other surrounding countries. Education, as a nondrug therapy for KOA recommended by both OARSI and ESCEO, is important for the treatment of patients with KOA [67], which can improve the living habits and relieve the pain of KOA. Although the thalamus is an important part of the pain matrix, previous studies have also found abnormal thalamus structure in patients with KOA [86]. However, the regulatory mechanism of thalamus and related brain regions involved in Tuina analgaesia remain unclear, especially the relationships amongst different brain tissues and the relationship between different brain tissues and clinical behavioural indicators, thereby limiting the promotion and application of Tuina. Therefore, fully exploiting the advantages of Tuina and evaluating the analgaesic effect and central mechanism are necessary to better alleviate the pain of KOA.

Multimodal MRI is a cutting-edge technology in the study of pain brain-network mapping and analgaesia mechanism. It can explore the mechanism of pain and evaluate and predict pain. It is extensively used in brain science and pain research. Brain MRI is one of the most commonly used neuroimaging technologies in the study of central mechanism given its advantages of its high-quality spatial resolution, no radiation, rapid imaging velocity, non-invasion, and affordable price [86–89]. The pathogenesis of chronic pain and persistent pain of KOA are closely related to the subcortical structures and morphological parameters of subcortical nucleus [22]. DTI can quantitatively measure diffusion tensor and FA to examine the microstructure and macrostructure of WM in vivo [90, 91]. fMRI is widely used in the clinical and theoretical studies of Tuina analgaesia for KOA [92], cervical spondylosis [45, 93], lumbar disc herniation [94, 95], low back pain [21], etc. [62, 96–98]. fMRI can also be used to reveal the central mechanism of Tuina analgaesia, which is related to the functional changes in amygdala, hypothalamus, nucleus accumbens, hippocampus, cingulate gyrus, and other areas [92, 96]. As a main type of fMRI, resting-state fMRI has the advantage of providing more comprehensive information than task-related fMRI on the functional architecture of the brain [99]. The cross-study on this frontier technology and Tuina can better explain the mechanism of analgaesia and solve the pain problem.

This clinical trial will study the multidimensional evaluation of KOA pain and evaluate the physical function, quality of life, mental status (the level of anxiety and depression), and influence of emotional state on brain activity. We will use a combination of clinical behaviour and multimodal MRI indicators such as brain-function indicators, brain-structure indicators (FA, MD, and GMV), and brain-network properties to perform confirmatory and interactive Tuina analgaesia research, which can fill the knowledge gaps in brain pivot analgaesia research in Tuina discipline in this field.

Furthermore, owing to the great difference between humans and animals, as well as the particularity of Tuina manipulation, verifying the central regulatory mechanism of Tuina intervention on KOA analgaesia in animal experiments is difficult because of too many uncontrollable factors. The application of multimodal MRI to Tuina discipline can clearly explore the brain central characteristics of KOA pain only in clinical trial, as well as comprehensively and deeply analyse the central analgaesic regulation mechanism of KOA patients with chronic pain after Tuina, which is a new trend in the future research of Tuina. We can also provide a reference experimental paradigm for the cross-study on the analgaesic effect of TCM nondrug therapy.

## Study limitations

This research has an inevitable limitation associated with the difficulty in controlling the methodology of blinding during the Tuina and healthcare education intervention, which cannot be blinded for the participants and therapists. Patients can know their group and anticipate the effect of the treatment in advance, which may affect their outcomes. For a study involving complex, multicomponent mind–body therapy, identifying a feasible, useful, and valid sham comparison group remains challenging, with no well-accepted solution.

## Trial status

This trial is recruiting patients now. Participant recruitment started in Sep. 2020 and is expected to end in Dec. 2022. The version of this protocol is the 1st version and the completion time is 8 Sep. 2020.

## Abbreviations

KOA: Knee osteoarthritis
VAS: The visual analogue scale
SF-MPQ: The Short-Form McGill Pain Questionnaire
HAMD: The Hamilton Depression Scale
HAMA: The Hamilton anxiety scale
WOMAC: The Western Ontario and McMaster Universities
SF-36: The Short From 36 Survey Questionnaire
